**Figure 3 figure3:**
[figure not shown]
Mobile app intervention material sample.

### Settings

Our research team will conveniently select 5 cities or counties in central and western China as research sites. Local hospitals or medical schools will provide assistance in the recruitment of participants and other implementation issues of the project. All researchers in this study were required to have a professional background in medicine or public health and received unified training conducted by the research team before the start of the study. This study is scheduled to start in September 2024 and is expected to last for about 12 months. This study was registered on the Chinese Clinical Trial Registry (ChiCTR 2300067402, registration date January 6, 2023).

### Ethical Considerations

The subjects of this study are 11-13-year-old girls’ parents who do not choose to get their daughters vaccinated against HPV. Due to the fact that HPV vaccination for children in China requires parental informed consent, we will only recruit parents instead of their daughters in this study.

In adherence to normative documents, including the Declaration of Helsinki (revised by the World Medical Association in October 2013) and the “Approach to the Ethical Review of Biomedical Research Involving Humans” issued by the National Health Commission of the People’s Republic of China, Research Ethics Committee, Chinese Academy of Medical Sciences & Peking Union Medical College, approved this research (ID: CAMS&PUMC-IEC-2022-077) on November 30, 2022, following thorough review and discussion. Informed consent will be obtained from all participants, with a clear explanation of the project, including confidentiality agreements and conditions for opting out at any time.

If parents accept the free HPV vaccination for their daughter, they will need to pay a Chinese yuan (CNY) 20 (~US $3) injection fee to the local health facility, which is the same as the injection fee for other vaccines. Participants will incur no additional costs by participating in this study. Additionally, they will benefit from learning about HPV, HPV vaccines, and cervical cancer prevention. Participants can choose to vaccinate their daughters with free HPV vaccines offered by the government or decline. This project aims to improve HPV vaccine coverage among girls aged 11-13 years in low-health-resource areas in China, provide valuable insights into promoting HPV vaccination nationwide, and, ultimately, contribute to reducing and potentially eliminating cervical cancer in China.

### Patient and Public Involvement

After project introductions by the researchers, those who are interested in this study will be recruited. Once participants sign the informed consent form, the researchers will complete eligibility checklists, and those who fail to meet the inclusion criteria will be removed. All information will be stored on an encrypted laptop. Participants will also have the right to freely obtain more information at any time and will be allowed to freely withdraw from the study without restrictions at any research stage.

### Sample Size

According to the purpose of intervention effect evaluation, the comparison formula of 2 independent rates is used to calculate the required sample size. To date, there are no studies on the effects of a mobile app–based intervention for 11-13-year- old girls in central and western China to improve the HPV vaccination rate. For this reason, the anticipated effect size is largely based on findings of similar studies derived from the relevant literature in other countries. In this study, according to the literature review and the results of our research team’s free HPV vaccination campaign conducted in Ordos City, Inner Mongolia Autonomous Region, China, in 2020, about 30% of parents in the control group refused to vaccinate their daughter (Pc), while parents in the intervention group who refused are expected to be 20% lower than those in the control group (Pt): α=.05 (2-sided), β=.2 [29-31]. Considering the possible dropout (20%), the intervention and control groups need 74 effective samples each, totaling 148, and each project site needs to recruit about 150 participants. There will be 750 participants in 5 project sites, 375 (50%) in the intervention group and 375 (50%) in the control group.

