## Methods

### Trial Design

This will be a double-blind randomized controlled trial (RCT) of an intervention based on an online applet. Before the intervention, the research team will carry out free HPV vaccination pilot projects for 11-13-year-old girls in 4-5 study sites in low-health-resource areas in China. After the first stage of the HPV vaccination program is completed, 11-13-year-old girls’ parents who choose not to vaccinate their daughters will be invited to our intervention study, and those who are willing to participate will be guided to register and log on to the “Yi Yan Health” mini applet (Figure 2), which was independently developed by our research team and can be used for mobile app–based education and questionnaire collection. Next, all participants will be randomly divided into 2 groups: (1) an intervention group, which will receive a baseline questionnaire, 7-day digital HPV vaccination education based on the IMB model (with a sample shown in Figure 3), and follow-up right after the intervention period and 1 week, 1 month, and 3 months after the intervention, and (2) a control group, which will only receive popular science education that is not related to HPV vaccines; these non-HPV publicity materials will be uploaded at the same time every day as the intervention group to maintain parents’ interest in the control group. Meanwhile, participants in the control group will also need to complete questionnaires simultaneously with the intervention group. After the intervention trial, we will provide the control group with the same IMB-based HPV vaccine intervention materials free of charge for ethical considerations. Our free HPV vaccination pilot program will also continue until at least half a year after the intervention to ensure that all 11-13-year-old girls whose parents are willing to vaccinate their daughters can receive the first HPV vaccination during or after the intervention.

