Evidence suggests that a change in behavior is the result of knowledge, psychology, and social factors, which indicates that the design of health education activities could be based on appropriate theories of behavior change [42,43]. The health intervention materials in this study are based on the IMB model, which improves the logicality and scientific integrity of the intervention. Our research team had previously used similar health education materials in an intervention for HPV vaccination willingness among female college students in mainland China, and the results revealed that the proportion of participants willing to receive HPV vaccines increased from 52.5% before the intervention to 59% after the intervention, while the proportion in the control group did not change [44]. These results indicate that the 7-day digital HPV vaccine education interventions based on the IMB model can improve the willingness of participants to receive HPV vaccines, which proves the effectiveness of mobile app–based education in female college students. Such effectiveness may be extended to other groups, such as parents of 11-13-year-old girls.

To the best of our knowledge, there is no research using the theory-based digital education method to improve the HPV vaccination rate among 11-13-year-old girls in central and western China. Regarding the study design, this double-blind RCT with the actual vaccine coverage rate as the main outcome may provide more innovative suggestions for the promotion of HPV vaccines. At present, because of the efforts of the Chinese government in infrastructure construction, mobile devices have become an integral part of daily life among the majority of Chinese people, including in central and western China. Additionally, mobile app–based interventions could be free from time and space constraints, greatly improving the efficiency and flexibility of interventions and reducing the cost, which can benefit more people. If this study proves that the 7-day digital HPV vaccine education intervention based on the IMB model can effectively improve the HPV vaccination rate, this convenient, low-cost, and easy-to-popularize intervention can be implemented among a wider range of people.

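### The sample size takes 30% refusal as the control-arm rate, but every randomised parent has already refused, so the stated 80% power does not describe the trial population

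*Protocol article*

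**What the plan says.** The Sample Size section uses the formula for two independent proportions. Its inputs are:

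- Control refusal: "about 30% of parents in the control group refused to vaccinate their daughter (Pc". The stated basis is a literature review together with the team's "free HPV vaccination campaign conducted in Ordos City, Inner Mongolia Autonomous Region, China, in 2020".
- Intervention refusal: "parents in the intervention group who refused are expected to be 20% lower than those in the control group (Pt".
- Error rates: "α=.05 (2-sided), β=.2".
- Attrition: "Considering the possible dropout (20" per cent).

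The result is that "the intervention and control groups need 74 effective samples each, totaling 148". That figure, rounded to about 150, is applied to each site and multiplied by five sites to reach 750, or 375 per arm.

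The enrolled population is described elsewhere. Under Trial Design, once the first stage of the free programme is over, "parents who choose not to vaccinate their daughters will be invited to our intervention study". Ethical Considerations, Eligibility Criteria and Recruitment say the same: a parent enters by having refused. The primary outcome is registry-verified vaccination of the daughter within 3 months after the intervention. The control arm receives health material unrelated to HPV vaccines.

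**The concern.** The rate used for the control arm appears to describe a different group from the one randomised. A vaccination campaign's refusal rate would normally be the share of offered parents who decline. Here, that share determines who can enter the trial; it does not say what those parents do afterwards. At entry, refusal is 100% by definition. The quantity the calculation needs is the proportion of those refusers who still have not vaccinated 3 months later.

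The power statement is the only place where the article says what size of effect the trial is built to find. If its control rate and its effect belong to another population, the 80% cannot be carried over to the primary comparison. Readers are then left without a design statement for the 750 parents who will be randomised.

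**Working it through.** **1. Reproduce the stated figure.** Inputs from Sample Size: Pc = 0.30; Pt = 0.10 (20 points lower); two-sided alpha 0.05 (z = 1.960); power 0.80 (z = 0.842); dropout 20%.

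Unpooled formula: n = (1.960 + 0.842)² × [Pc(1 − Pc) + Pt(1 − Pt)] / (Pc − Pt)² = 7.849 × (0.21 + 0.09) / 0.04 = 58.9, so 59 per arm.

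Dropout: 59 / (1 − 0.20) = 73.75, so 74 per arm and 148 in total. This matches exactly, so 30% and 10% are the operative inputs. Reading the 20% as relative (30% v 24%) would need at least 856 per arm before dropout and does not reproduce the figure.

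**2. Translate the inputs into the primary outcome.** Everyone randomised has refused, so uptake at 3 months is 1 − refusal:

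- Control: 1 − 0.30 = 70% of prior refusers vaccinate on non-HPV material.
- Intervention: 1 − 0.10 = 90% of prior refusers vaccinate.

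No section reports later uptake among parents who first declined, so neither figure has a source in the article.

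**3. What 750 delivers in a refuser population.** The article gives no uptake rate for prior refusers. The control values below (5, 10, 20 and 30%) are therefore assumptions, shown as a range. Power uses the pooled variance under the null, with p̄ the mean of the two rates and n per arm:

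power = Φ{ [ |p1 − p2|√n − 1.960√(2p̄(1 − p̄)) ] / √(p1(1 − p1) + p2(1 − p2)) }

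Completers per arm after 20% loss: 375 × 0.80 = 300.

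| Assumed control uptake | Detectable uptake at 80% power, 300 per arm | Detectable uptake at 80% power, 375 per arm | Power for 20 points, 300 per arm | Power for 10 points, 300 per arm |
|---|---|---|---|---|
| 5% | 11.2% | 10.5% | >99.9% | 98% |
| 10% | 17.9% | 17.0% | >99.9% | 93% |
| 20% | 29.9% | 28.8% | >99.9% | 81% |
| 30% | 40.9% | 39.7% | 99.9% | 73% |

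Check of one cell (control 10%, 300 per arm, intervention 17.9%): p̄ = 0.1395; numerator 0.079 × 17.32 − 1.960 × 0.490 = 1.368 − 0.960 = 0.408; denominator √(0.090 + 0.147) = 0.487; 0.408 / 0.487 = 0.84; Φ(0.84) = 0.80.

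With 300 per arm, the smallest detectable differences are 11.2 − 5 = 6.2, 17.9 − 10 = 7.9, 29.9 − 20 = 9.9 and 40.9 − 30 = 10.9 points, that is, about 6 to 11 points.

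**4. The per-site figure for comparison.** With 59 completers per arm, power for a 20-point difference is 87, 78, 66 and 60% at control uptake of 5, 10, 20 and 30%. The stated 80% for 148 participants therefore depends on the control rate assumed, while the 750-participant trial is insensitive to it at 20 points.

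**The case against.** **The denominator is not stated.** The article never says that the 30% refers to all parents offered the vaccine, and its cited sources are not to hand. This stands: the denominator is an inference from a general campaign. The point survives it, because nothing says the figure refers to prior refusers, and the 70% and 90% uptake it implies are unsupported whichever denominator was meant.

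**The uncertainty is disclosed.** Limitations concedes that the calculation cannot be exact because regional vaccination and hesitancy rates are lacking. That is uncertainty about a regional rate. If the 30% is a campaign refusal rate, knowing it exactly would still say only who becomes eligible, not how many refusers later change their minds.

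**The trial is large enough anyway.** This also stands, and it limits the point. A reader might infer that the trial is underpowered. The figures do not show that: the 80% was derived for 148 participants, and 750 are planned.

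It is also tempting to use the team's earlier result, in which willingness "increased from 52.5% before the intervention to 59% after the intervention", as the realistic effect and to compute power for 6.5 points. The article does not support that use. The figure is a change in willingness among female college students; it does not measure vaccination by parents who had refused.

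Nor does the mismatch affect the type I error rate. The two-sided 5% level does not depend on the planning rate, and the completed trial can still be read from its estimate and confidence interval.

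**Conclusion.** The point holds as a fault in the sample-size justification. The arm rates of 30% and 10% refusal cannot be squared with a trial that admits only refusers unless 70% of control parents reverse their decision without HPV education, which nothing in the article supports. The stated 80% power therefore does not describe the randomised population, and the planned 375 per arm carries no power statement.

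The practical size is moderate. Across assumed control uptake of 5 to 30%, 300 completers per arm keep at least 99.9% power for 20 points. Power drops below 80% only for differences smaller than about 6 to 11 points, depending on control uptake. These figures rest on the assumed uptake range, 20% loss and a simple two-proportion comparison. Whether an effect that small is likely cannot be judged from the article.

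**What to change.** Rewrite the Sample Size paragraph as follows:

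- Replace Pc and Pt with an assumed 3-month vaccination uptake among prior refusers. Label it as an assumption and show it over a range such as 5 to 30%.
- State what the fixed 750 delivers: the smallest uptake detectable with 80% power at 300 and at 375 per arm, as tabulated above.
- Add that a 20-point difference keeps at least 99.9% power after 20% loss over that range, and that power falls below 80% only for differences smaller than about 6 to 11 points.
- Keep the 30% only as the expected share of offered parents who become eligible, and only if the sponsor confirms that this is its denominator.

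The cost is one paragraph. Enrolment, randomisation, outcome and analysis do not change.

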### Eligibility Criteria

The inclusion criteria are as follows:

Parents who have refused to vaccinate their 11-13-year-old daughters against HPV after being offered the first dose of vaccinationParents who have the local household registration of the research siteParents who have an electronic device with internet access, such as a smartphone, a tablet, or a laptopParents who are able to read and understand the questionnaireParents who understand the vaccination procedure and volunteer to participate in this study

The exclusion criteria are as follows:

Parents whose daughters have contraindications for HPV vaccination or other physical conditions that are not suitable for HPV vaccinationParents who have participated in similar research in the past 6 months

### Recruitment

In 5 regions with free HPV vaccination pilot projects, parents who refuse to vaccinate their daughters and who meet the inclusion criteria will be enrolled into this study. After providing informed consent, all participants will register and log on to the mini applet, and they will then be randomly assigned to the intervention group or the control group in a 1:1 ratio using the randomization algorithm embedded in the mini applet.

### Intervention

#### Intervention Group

All participants in the intervention group will need to log on to the mini applet through a computer or a smart phone and will receive 7-day digital HPV vaccination education based on the IMB model. Our research team has developed intervention materials after reviewing the relevant literature and conducting multiple rounds of panel discussions with a group of experts, including 1 cancer epidemiologist, 1 infectious disease epidemiologist, 1 researcher from the project center, and 1 senior manager from a media company. This 7-day digital HPV vaccination education intervention was previously applied by our research team in a project on HPV vaccination willingness of Chinese female college students and achieved positive results [14,32]. However, since digital education aims to target different participants in this study, the researchers have worked with the expert panel to adjust and optimize the previous content to better meet the needs of the parents of 11-13-year-old girls before the start of intervention.

According to the IMB model, digital HPV vaccination education is divided into 3 modules and 6 themes, with each module containing 2 themes. The first module is information, which is the initial prerequisite for promoting healthy behaviors. Module 1 has 2 themes: (1) HPV infection and related diseases and (2) high-risk factors of HPV infection and how to prevent HPV infection. The second module is motivation, which mainly refers to personal attitudes toward health behavior and related social motivation. Personal attitudes include the understanding of HPV susceptibility, the expectation of costs and benefits of taking preventive actions, and the experience and willingness to take actions; social motivation includes social support and social values. Module 2 has 2 themes: (3) introduce the benefits of HPV vaccines so as to encourage parents to vaccinate their daughters and (4) describe the harm and susceptibility of HPV infection through a true story to motivate parents to take action to prevent their daughters from contracting HPV infection. The third module is behavioral skills, which mainly emphasizes the improvement of personal objective skills and self-efficacy. Module 3 has 2 themes: (5) how to use personal objective skills to make firm decisions and communicate effectively with family members to obtain understanding and support for daughters’ HPV vaccination and (6) the concept and function of self-efficacy and ways to improve self-efficacy and promote the transformation of motivation into behaviors.

Each of the 6 thematic courses will be uploaded to the mini applet and will take participants about 10-15 minutes to read and learn. In addition, the mobile app–based HPV vaccination education contains a high level of interactivity with the following learning forms: reading text, viewing pictures, small videos pictures watching, and taking quizzes. The intervention will last for 1 week, and data will be collected at baseline ( 1 week before the intervention); postintervention; and 1 week, 1 month, and 3 months after the intervention. All the data will be obtained for statistical analysis.

#### Control Group

The control group will receive health promotion materials unrelated to HPV vaccines, and the researchers will distribute the questionnaire to both intervention and control groups simultaneously through the same mini applet. After 3 months of follow-up, participants in the control group will receive the same health education about HPV vaccines as the intervention group, free of charge for ethical considerations.

### Adherence

The intervention will be stopped at the participants’ request if they find anything harmful about it, and participants have the right to refuse to answer some sensitive questions in the questionnaire or to withdraw from the study at any time.

Before the intervention, the researchers will introduce the importance and expected benefits of this study. During the intervention, once the course is uploaded, the mini applet will automatically send a text message to participants every day to remind them to learn until they have completed the course. The researchers can also supervise participants by their learning duration, which will be automatically recorded by the backend database of the mini applet. During follow-up, similarly, the mini applet will automatically send a text message to participants every day before they complete the questionnaire, and the number of completed questionnaires will be used to evaluate the adherence of participants to the entire trial process. Finally, we will express our gratitude to all participants for their involvement and encourage them to complete the study through nonmaterial incentives, such as by answering their questions related to HPV or cervical cancer during the research.

### Measures

#### Outcome Measurements

The questionnaire in this study is divided into 4 sections: general demographic data, current HPV vaccination status, parents’ hesitancy and attitudes toward HPV vaccines, and potential factors related to HPV vaccine hesitancy. The questionnaire in the study is designed in Chinese to ensure that participants can understand and respond to the questions.

#### Primary Outcome: HPV Vaccination Status

The ultimate goal of this study is to improve the HPV vaccination rate among 11-13-year-old girls. This indicator will be measured by the proportion of parents who choose to vaccinate their daughters against HPV within 3 months after the intervention. To ensure the authenticity of HPV vaccination, the vaccination status will be checked by the registration history in the information systems of local health agencies, which have already collaborated with us, rather than being self-reported by participants. The HPV vaccination behaviors will be strictly verified by our researchers, and those who are just “willing” to be vaccinated will not be included in the positive results.

#### Secondary Outcomes: Parents’ Hesitancy and Attitudes Toward HPV Vaccines

We will measure parents’ hesitancy and attitudes toward HPV vaccines in 3 parts. The first part is about general vaccination attitudes, which will be used to investigate participants’ attitudes toward other common vaccines recommended by the Chinese government. The second part is about HPV vaccine hesitancy, which will be used to assess the degree of HPV vaccine hesitancy among parents. The third part is about vaccine confidence used, which will be to investigate participants’ confidence in HPV vaccines.

